**WP 7: Motor Skills and Effects on Executive Functions**

### Background

It is well established that cognitive ability is a powerful determinant of success in many aspects of social and economic life (e.g. Cunha and Heckman 2007; Duckworth et al. 2011). However, more recent research suggests that non-cognitive abilities (e.g. conscientiousness, grit, and self-control) in early life are at least as important as cognitive abilities for later outcomes such as school readiness and educational careers (e.g. Duckworth et al. 2011). Based on recent literature on child development, Cunha and Heckman (2007) found that non-cognitive abilities have direct effects on wages (controlled for schooling), teenage pregnancy, smoking, crime, performance on achievement tests and many other aspects of social and economic life.

The concept of ‘non-cognitive skills’ has been used broadly about skills other than academic skills such as literacy and numeracy. We focus on the link between motor skills and one important aspect of non- academic skills: executive functions, which cover both working memory (which is related to IQ) and inhibitory control, which includes inhibition of thoughts, attention and behaviour (Almlund et al. 2011; Diamond 2014a). We focus on executive functions because most prior work on the non-academic effects of motor skills interventions focuses on executive functions. Within executive functions, we focus on inhibitory control because it is related to concepts such as conscientiousness and self-control that are highly predictive of many long-term outcomes (see Almlund et al. 2011 for a comprehensive review of this literature). Among the big five personality traits, conscientiousness is the strongest predictor of long-term outcomes (Heckman and Kautz 2012). It has been defined as “consistency of action resulting from deliberate volition, or will” (Almlund et al. 2011, p. 10). Conscientiousness is a measure of whether the child manages to accomplish more work, makes an effort, pushes her/himself hard to succeed, is good at organizing, is good at avoiding distractions, does not put off unpleasant tasks, makes careful decisions, is goal-oriented, does not give up easily, remains calm under pressure and the like (MacCann et al. 2009).

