### Variables

*Predictors:*

Gross and fine motor skills as described in the main protocol.

*Outcomes:*

The Preschool Self-Regulation Assessment Battery (PSRA)

The PSRA was designed to assess self-regulation in emotional, attentional, and behavioural domains by using a brief, structured battery of tasks in conjunction with a global report of children’s behaviour. This test can easily be translated into Danish. It includes balance beam and pencil tapping. Age span: 3-5 years. Time consumption: Four brief tasks; 8-10 minutes (Smith-Donald et al. 2007).

Academic performance

Academic performance will be assessed based on the Grade 9 school examinations school grades and the Danish National Test. The Danish National Tests are described in work package 5. Grades from all six subjects in the Danish National Test from Grade 2 to Grade 8 will be used.

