### Covariates,

The following covariates will be accounted for when analysing the results: sex, age, socioeconomic status, baseline estimated general intelligence and child wellbeing.

Reynolds Intellectual Screening Test (RIST)

RIST is developed to provide a quick and reliable measure and is used to measure an estimated general intelligence at baseline. The RIST consist of two of the subtests from Reynolds Intellectual Assessment Scale (RIAS). The four RIAS subtests to measure general intelligence include two nonverbal tests and two verbal tests. The RIST consists of one verbal test (Guess what) and one nonverbal test (Odd item out). The test is appropriate for individuals ages 3 to 94. The median reliability coefficient for the RIST Index is .95 and the test-retest reliability is .84 (Reynolds & Kamphaus, 2003). RIAS has been found to correlate highly with the other assessments of general intelligence (Edwards & Paulin, 2007) and there is a high correlation between RIST and RIAS (Reynolds & Kamphaus, 2003).

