### Length of follow-up,

The duration of the follow-up period is six months to three years (preschool period)

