### Analyses

Simple univariate statistics will be calculated to describe the outcomes and covariates by school.

Multilevel linear regression models will be constructed to assess the effectiveness of the intervention on executive functioning. The baseline value of the outcome variable, time since baseline, intervention group and the covariates of sex, age, estimated general intelligence, socioeconomic status of the household and child well-being at baseline will be added to the model along with school and socioeconomic status of the area as random effects. The interaction between school and intervention group will be tested. The assumptions for the models will be checked.

Similarly multilevel linear regression models will be constructed to assess the effectiveness of the intervention on academic performance as measured by the Grade 9 examination grades. The baseline value of the outcome variable, time since baseline, intervention group and the covariates of sex, age, estimated general intelligence, socioeconomic status of the household and child well-being at baseline will be added to the model along with school and socioeconomic status of the area as random effects. The interaction between school and intervention group will be tested. The assumptions for the models will be checked.

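### The WP 7 Grade 9 model repeats the preschool model's time-since-baseline term and may thereby condition on school progression after randomisation; direction and size of any bias are unknown

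*Protocol*

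**What the plan says.** WP 7 specifies two multilevel linear models with the same covariate list, one for executive functioning and one for school results. The second concerns "academic performance as measured by the Grade 9 examination grades. The baseline value of the outcome variable, time since baseline, intervention group", followed by "the covariates of sex, age, estimated general intelligence, socioeconomic status of the household and child well-being at baseline". The Covariates section of WP 7 lists plain age, without saying when it is taken: "sex, age, socioeconomic status, baseline estimated general intelligence and child wellbeing".

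The Variables section gives the source of the outcome: "Academic performance will be assessed based on the Grade 9 school examinations school grades and the Danish National Test". The follow-up section does not reach that far: "The duration of the follow-up period is six months to three years (preschool period". Nothing in WP 7 defines time since baseline for a Grade 9 result, and late school start and grade repetition are not mentioned.

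The Background of WP 7 describes non-cognitive abilities in early life as "at least as important as cognitive abilities for later outcomes such as school readiness and educational careers". Objective 1 aims to improve skills of this kind, self-control and inhibitory control. Objective 2 asks for the effect of the intervention on academic performance.

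**The concern.** In the executive-function model children are measured after follow-up of differing length, so a time term does useful work. A Grade 9 examination is tied to a school grade. Time since baseline is then not a planned length of follow-up. It records when the child arrived at Grade 9.

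Given age at baseline, part of that timing is fixed before randomisation (where the birth date falls relative to the school-year cut-off). The other part is settled afterwards, by starting school late or repeating a grade. The protocol's own background connects the targeted skills with readiness for school and later schooling, so the second part could be a consequence of the intervention. Holding it fixed would mean that the group coefficient no longer estimates the total effect on academic performance, which is what objective 2 seeks.

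**Working it through.** The plan gives no effect size, rate of delay or power figure for this analysis, so there is no stated figure to reproduce. Two checks were made.

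**1. What the two terms amount to.** Let T be group, A age at baseline, S time since baseline and E age at the examination, so E = A + S. Then

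b·T + c·A + d·S = b·T + (c − d)·A + d·E.

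The coefficient b is the same in both forms: adjusting for A and S is adjusting for A and E. This requires age to be age at baseline. In the simulation below the two versions gave the same group coefficient to four decimals in all 36 scenarios.

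**2. Whether the term changes the group coefficient.** All inputs are assumptions; none comes from the protocol.

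- 1,000,000 children per scenario, 1:1 allocation, one common baseline date, ages 3 to 6.
- Delay D (one year): logit P(D = 1) = logit(p) − s·U + λ·T, with p = 5% or 15%; λ = 0, −0.3 or −0.7; U unmeasured ability; s = 0 or 0.8.
- Examination date = nominal school-year date + D.
- Grade: Y = 0.10·T + 0.6·U + γ·D + 0.8·ε, with γ = −0.3, 0 or +0.3. Apart from T and D the SD is √(0.36 + 0.64) = 1.
- Least-squares group coefficient with T and A, and with T, A and S. Clustering was left out; it bears on standard errors rather than on which variable is held fixed.

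This gives 2 × 3 × 2 × 3 = 36 scenarios.

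| Scenarios | Without S | With S | Change |
|---|---|---|---|
| No effect on delay (12) | about 0.10 | about 0.10 | at most 0.0003 in size |
| Delay reduced, p = 5%, largest fall | 0.1113 | 0.1022 | −0.0091 |
| Delay reduced, p = 5%, largest rise | 0.0923 | 0.0947 | +0.0024 |
| Delay reduced, p = 15%, largest fall | 0.1216 | 0.0881 | −0.0335 |
| Delay reduced, p = 15%, largest rise | 0.0775 | 0.0896 | +0.0121 |

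The largest fall is 0.0335/0.1216, about 28%; the largest rise is 0.0121/0.0775, about 16%. Of the 24 scenarios in which the intervention reduced delay, the estimate fell in 16, rose in 4 and did not move in 4. Those last 4 are the ones in which delay had no association with grades (s = 0 and γ = 0). So the term matters only if the intervention alters progression and progression is associated with grades. The grid does not cover an intervention that increases delay.

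A second set of assumptions sends the whole effect through readiness (0.2 SD), with 5% to 15% delayed and a correlation of 0.3 to 0.7 between readiness and the liability to delay. The estimate then shrinks by 1% to 13%. At 10% delayed and correlation 0.5 it goes from 0.102 to 0.097, that is 0.005/0.102, about 5%.

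**The case against.** A reader might infer that part of the effect is removed, or that the estimate is biased towards zero. The documents do not support that. They give no rate of late start or repetition and no effect of the intervention on either. The background sentence links the skills to later schooling in general terms only. Consistent shrinkage appears where the whole effect is assumed to run through readiness; under the broader assumptions the estimate could also rise or stay put. This objection stands in full and limits the conclusion.

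Three further points stand in part.

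- The wording does not settle that age is age at baseline, since the closing words of the list may attach to well-being alone. If age meant age at the examination, the model would adjust for that variable directly, and deleting the time term alone would not cure it. The fix must therefore name the age.
- The division of the timing into birth-date position and delay assumes a common baseline date. The schedule is in the main protocol, which is not at hand. If baseline dates differ, the term also carries date of entry.
- The term holds some prognostic information from before randomisation, so removing it without a replacement could cost precision.

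It may also be said that the covariate set for so distant an outcome is a matter for a statistical analysis plan. But this protocol names the covariate outright, so the point concerns a stated choice rather than an omission.

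**Conclusion.** The point holds as a minor one. The Grade 9 model takes over a term that serves no follow-up-length purpose for an outcome fixed to a school grade, and it may condition on a consequence of the intervention. Any bias in the total effect is of unknown direction and size. There is none if the intervention does not alter school progression. The simulated range of −0.034 to +0.012 around an assumed direct effect of 0.10 illustrates what is possible and is not an estimate for this trial. The reading of the two terms as age at the examination rests on age being age at baseline.

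The same model also asks for a baseline value that Grade 9 grades cannot have in preschool children, and the stated WP 7 follow-up ends in preschool. These are separate matters, but they fit a covariate list carried over without adaptation.

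**What to change.** In the Grade 9 model of WP 7:

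- delete time since baseline;
- state that age is age at baseline;
- add birth date relative to the school-year cut-off, that is, position within the school year. This keeps the prognostic information that precedes randomisation. Raw birth date would only duplicate baseline age if all children share one baseline date;
- if the data are available, report late school start or grade repetition by arm as a descriptive result.

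The time term can stay in the executive-function model. The cost is a short change of wording and no change to the trial's main data collection. The one downside is a possible small loss of precision if the birth-date term is not added.

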# WP 8: Associations between motor skills, physical activity, cognition, psychological wellbeing and language development for children at developmental risk.

**Background**

Developmental difficulties, such as, but not limited to, Intellectual Disability (ID), Downs syndrome (DS), Cerbral Palsy (CP), Autism Spectrum Disorders (ASD), and Attention Deficit Hyperactivity Disorder (ADHD), are associated with motor performance difficulties. Developmental difficulties are further associated with different patterns of participation in both daily physical and play activities [1,2].

Motor skill difficulties may in themselves function as a barrier to physical activity. However, other factors related to developmental difficulties have been found to impose further psychological, practical, social and societal barriers to participation [1,3]. Examples of these barriers are related social difficulties, behavioral problems, exclusion, strain on family or staff, other constraints on family time and resources, a higher need for adult supervision as well as lack of skills to include the children [1,2,3]. The number of parent-reported barriers to physical activities have been directly linked to both hours spent in physical activity as well as total screen time [3]. The patterns of participation in daily physical and play activities influence the child’s opportunities to develop both motor and social skills and over time further reduce the child’s opportunities to gain positive experiences with these activities. Possible facilitators that may support physical participation for children with developmental difficulties are currently being identified in practice [4] and programs adapted to children and adolescents with developmental difficulties are being developed, one example in Denmark being FOKUS [5]. In FOKUS, shooting sports are made available to children and adolescents with ADHD and similar developmental difficulties through collaboration between the Danish Society for Gymnastics, municipalities and schools [5]. The aim is to increase the opportunities for participation in organized sports activities. Current research evidence suggests that physical activity may be an effective non-pharmaceutical intervention approach for children with developmental disorders [1] and may help improve sleep quality [6], reduce stereotypical behaviors [7] and reduce behavioral problems [8]. Understanding the extent to which physical activity alters developmental trajectories of mental health is of increasing importance [1].

A motor skills intervention may be of particular importance for children at early developmental risk and, if effective, may be associated with larger overall improvements.

### Objectives to be explored in the RCT

1. To estimate the effect of a motor skills intervention on motor skills, physical activity, cognition, language development and wellbeing for a subgroup of children at early developmental risk.
2. To look at specific barriers to, and facilitators of, participation of children at early developmental risk in the motor skills program.

### Objectives to be explored in the cohort study

1. To establish potential patterns of development of motor skills, physical activity, cognition, language development and wellbeing from three to fifteen years of age for a subgroup of children at early developmental risk.*
2. To determine the influence of motor skills, physical activity, verbal development, social-emotional development, early developmental concerns and wellbeing on developmental difficulties in adolescence.*

** long-term follow-up (12 years)*

### Variables

A subgroup of children will be included in the sub-group of children at early developmental risk based on the following information and measures:

- - Information on early medical and psychiatric diagnoses is collected from parents at baseline and at the last follow-up before starting school. Afterwards, this information is collected yearly during the school years.
  - Strengths and Difficulties Questionnaire (SDQ) is completed as described in WP 6. Computerized algorithms have been developed to estimate the likelihood of a child’s having a psychiatric diagnosis based on symptom and impact scores derived from the SDQs [9]. These algorithms are used to generate likelihood ratings (either: unlikely, possible or probable) for four broad categories of disorder: conduct disorders, emotional disorders, hyperactivity disorders and any psychiatric disorder. The algorithm has been found to correctly identify 81-91% of children who definitely had the indicated clinical diagnosis and is described as sufficiently accurate and robust

to be of practical value [9]. In this study, a probable rating of any of the four categories of disorders is seen as an indicator of a probable developmental disorder and henceforth as early developmental risk.

Further, information on the children’s early social-emotional development and the staff observations of the children’s wellbeing will be collected in the Municipality of Svendborg in the same period. Staff evaluations of child wellbeing are systematically collected twice yearly following written guidelines for the evaluation [10]. Part of this evaluation is the discussion of four domains of child wellbeing (psychological and emotional, cognitive, social and physical). Based on these discussions, a rating of thriving, cause for concern or strong concern is made for the overall wellbeing of each child. These registrations will be available for the study.

Thus, the child is perceived as being at early developmental risk if:

- - Parents report having received a formal child psychiatric diagnosis for the child prior to or during the project period.
  - Parents report having received a formal medical diagnosis for the child, during the project period. The focus is on pervasive diagnosis such as deafness, CP and DS which is known to influence development more pervasively.
  - The SDQ algorithm indicates the likelihood of a psychiatric disorder on the basis of either the completed parent or staff questionnaire.
  - Staff rate high developmental concern in the RCT period.

The child is perceived as having developmental difficulties (as an outcome) if:

- Parents report having received a formal child psychiatric diagnosis for the child.
- Parents report having received a developmentally pervasive medical diagnosis for the child.
- The SDQ algorithm indicates the likelihood of a psychiatric disorder on the basis of the completed child, parent or teacher questionnaire at the last point of data collection.

This broad inclusion and practical demarcation of developmental difficulties is used in order to get a broader understanding of the developmental mechanisms related to children at developmental risk.

The following covariates will be accounted for when analyzing the results: sex, age, socioeconomic status as well as estimated general intelligence and executive functions as described in WP 7.

Barriers and facilitators:

Barriers to, and facilitators of, implementation in relation to children at early developmental risk are investigated using observations of participation from the perspective of the child [13]. Child participation will be observed in different preschools, both in activities defined as part of the motor skills intervention as well as in a number of other activities. Further, semi-structured qualitative interviews [14] with staff in the preschools will be included to strengthen the understanding of potential barriers and facilitators associated with children at early developmental risk.

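### WP 8 accepts psychiatric diagnoses made before entry but ties the medical criterion to the project period, so some children already diagnosed with the conditions it names can miss the at-risk subgroup

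*Protocol*

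**What the plan says.** All of this stands in the protocol, WP 8, Variables. The list of criteria for early developmental risk has four entries:

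- Psychiatric diagnosis: "Parents report having received a formal child psychiatric diagnosis for the child prior to or during the project period".
- Medical diagnosis: "Parents report having received a formal medical diagnosis for the child, during the project period". The next sentence names the target: "The focus is on pervasive diagnosis such as deafness, CP and DS which is known to influence development more pervasively".
- SDQ: "The SDQ algorithm indicates the likelihood of a psychiatric disorder on the basis of either the completed parent or staff questionnaire".
- Staff rating: "Staff rate high developmental concern in the RCT period".

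The list does not say whether one criterion is enough, but the entries read as alternatives.

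Three other statements in the same section bear on the medical entry. On data collection: "Information on early medical and psychiatric diagnoses is collected from parents at baseline and at the last follow-up before starting school". On the later outcome of developmental difficulties, the medical part is "Parents report having received a developmentally pervasive medical diagnosis for the child", with no time limit. On intent: "This broad inclusion and practical demarcation of developmental difficulties is used in order to get a broader understanding".

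**The concern.** Two neighbouring criteria carry different time windows, and no reason is given. The narrower window is on the medical criterion, whose named conditions are the ones most likely to be known before a child enters at about age three. A child with DS recognised from birth is the plainest example. Read as written, the medical criterion turns that child away and keeps a child whose diagnosis happens to fall after entry.

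The subgroup carries much of WP 8. Both RCT objectives and the first cohort objective concern children at early developmental risk, and the Analyses section repeats the analyses of the other work packages within that subgroup. If the rule drops some clear cases, the results describe a somewhat different group from the one the WP 8 background introduces, which lists DS and CP by name.

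**Working it through.** No sample size, power or error rate depends on this rule, and the plan gives no figure to reproduce. The check is a comparison of texts.

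**Step 1: the windows side by side (WP 8, Variables)**

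| Item | Diagnosis before entry | Diagnosis during the project |
| --- | --- | --- |
| Psychiatric criterion | counts | counts |
| Medical criterion, literal reading | does not count | counts |
| Baseline parent report | collected, medical and psychiatric | not applicable |
| Medical part of the outcome definition | counts (no limit) | counts (no limit) |

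The medical criterion is the only row that shuts out earlier diagnoses.

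**Step 2: the rule applied to typical children.** I take any one criterion as sufficient.

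| Child | Rule read literally | Medical window matched to the psychiatric one |
| --- | --- | --- |
| DS, CP or deafness diagnosed before entry, no other criterion met | not in subgroup | in |
| Same diagnosis before entry, SDQ rating probable | in (SDQ) | in |
| Same diagnosis before entry, staff rate high concern | in (staff) | in |
| Same diagnosis before entry, plus a psychiatric diagnosis | in (psychiatric) | in |
| Medical diagnosis first made during the project | in (medical) | in |

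Only the first row changes. The affected children are those with an earlier medical diagnosis and nothing else that qualifies them.

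**Step 3: can the first row be populated?** The SDQ algorithm rates conduct, emotional, hyperactivity and any psychiatric disorder. The staff rating summarises overall wellbeing as thriving, cause for concern or strong concern. Neither is built to detect deafness, CP or DS. A deaf child, or a child with CP, who is thriving and has no probable psychiatric rating would fall into the first row.

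**Step 4: consistency with the outcome.** For that child, the same diagnosis does not count as early risk but does count later as developmental difficulty. The second cohort objective relates early developmental concerns, among other factors, to that outcome, so the two definitions ought to treat the diagnosis alike.

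**Step 5: size.** Let p be the share of children with such a diagnosis, e the share of these diagnosed before entry, and r the share of those who enter by another route. Then

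children lost per 1,000 = 1,000 × p × e × (1 − r).

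The protocol gives none of p, e or r. Purely as an assumption, take p = 0.3 to 1% and e = 80 to 100%. The product before the last factor runs from 1,000 × 0.003 × 0.80 = 2.4 to 1,000 × 0.01 × 1.00 = 10. Since r may lie anywhere from 0 to 1, the loss is between 0 and 10 per 1,000. This suggests a small number but does not estimate it.

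**The case against.** The strongest reply is that the other three criteria catch these children. Staff ratings are made twice a year and rest on a discussion of cognitive, social and physical as well as emotional wellbeing, where a pervasive condition could well show. This stands in part. A reader might infer that every child with DS, CP or deafness known at entry is excluded from the subgroup, and the document does not support that: such a child fails one criterion of four. But if the other routes were sufficient, a separate medical criterion would not be needed.

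A second reply rests on the comma in the medical entry, which allows the time phrase to describe when parents report. A diagnosis made earlier but reported at baseline would then count. That is grammatically possible and fits the baseline collection and the stated breadth. It fits poorly beside the psychiatric entry, where the corresponding phrase includes the time before the project. Parents report only from baseline onwards, so there the phrase must describe when the diagnosis was made. If the ambiguity is granted, two analysts could form different subgroups, and the same correction is needed.

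Third, the consequences are easily inflated. A reader might infer that the criterion loses 80 to 100% of its target group. That figure only repeats an assumption about age at diagnosis and ignores the other routes. A reader might also infer that the lost children contaminate a not-at-risk comparison group, or that the medical criterion would select nobody in the RCT. The protocol describes no such contrast, and it does not restrict RCT membership to baseline information. These parts of the reply stand in full.

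**Conclusion.** The membership rule is wrong as written, within narrow limits. The medical window is shorter than the psychiatric one without explanation. It conflicts with the criterion's own named conditions, the baseline collection of medical diagnoses, the declared breadth of the definition and the unrestricted outcome definition. This is not a detail left for a later analysis plan, because the protocol already states the rule.

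The loss is confined to children diagnosed before entry who meet no other criterion. Their number cannot be estimated from the protocol and is probably small. The omission turns on a fact that precedes the intervention and applies equally to both arms, so it does not disturb their comparability. The WP 1 primary outcome is untouched. What changes is whom the WP 8 subgroup results describe.

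The conclusion assumes that the four criteria are alternatives and that the time phrase refers to the diagnosis. That many of the named conditions are diagnosed before entry is plausible for DS and an assumption for CP and deafness. The textual conflict does not depend on it.

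**What to change.** In WP 8, Variables, reword the medical criterion so that it accepts a formal, developmentally pervasive medical diagnosis made either before the project or during it, as the psychiatric criterion does. Take the earlier diagnoses from the baseline parent report. If the difference between the two windows is intended, state the reason. Add one sentence saying that meeting any one of the four criteria places a child in the subgroup.

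The cost is one changed phrase and one added sentence. The baseline report is already planned, so no new data or procedure is needed.
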